# Efficacy and safety of Yirui capsule in patients with hyperlipidemia: study protocol for a multicenter, randomized, double-blind, placebo-controlled trial

**DOI:** 10.1186/s13063-016-1419-9

**Published:** 2016-06-18

**Keywords:** Hyperlipidemia, Chinese medicine, Yirui capsules, Randomized controlled trial

## Abstract

**Background:**

Hyperlipidemia is a common disease in China. Although 88.9 % of the Chinese population taking lipid-lowering medications has already used a statin, only 61.5 % of the population has reached the goal of low-density lipoprotein cholesterol. Thus, many patients in China seek help from Traditional Chinese Medicine. Yirui capsules are an innovative Chinese Medicine which are designed to improve the blood lipid state in patients with hyperlipidemia. However, there is still a lack of high-quality evidence from clinical trials to support the application. Therefore, we designed a clinical trial to evaluate the safety and efficacy of Yirui capsules for use by patients with hyperlipidemia.

**Methods/design:**

This is a multicenter, randomized, double-blinded, placebo-controlled trial. Based on lifestyle modification therapy, eligible patients will randomly be assigned to the Yirui capsule or the placebo group. The primary outcome is the percentage of participants who reach the goal of 30 % low-density lipoprotein cholesterol decline at treatment end-point. The secondary outcomes include the changes from baseline to treatment endpoint in low-density lipoprotein cholesterol, total cholesterol, triglyceride, high-density lipoprotein cholesterol, apolipoprotein A, apolipoprotein B, non-high-density lipoprotein cholesterol, MOS 36-Item Short-Form Health Survey scoring, total and individual item scoring of symptomatic grading and quantifying scale, and body mass index.

**Discussion:**

The main ingredients of the Yirui capsule are perilla oil, *Folium Ginkgo* (Yinxingye), *Radix Salviae miltiorrhizae* (Danshen), *Fructus Crataegi* (Shanzha), *Rhizoma Alismatis* (Zexie), and *Radix Notoginseng* (Sanqi), which are expected to improve the blood lipid state. This randomized placebo-controlled trial will comprehensively evaluate the effectiveness and safety of Yirui capsules against hyperlipidemia in the hope of providing a new adjunctive Chinese medicine option for clinical practice in dyslipidemia treatment.

**Trial registration:**

ChiCTR-IOR-15006496. Registered on 29 May 2015.

**Protocol version:**

WXJ.YRJN-HBT-V1.0 (21 Jan 2015).

## Background

Due to the unhealthy lifestyle of modern society, hyperlipidemia has become a common disease in China. According to the latest epidemiological research, more than 300 million adults in the Chinese population aged ≥20 years have a total cholesterol (TC) level ≥5.18 mmol/L and approximately 200 million people have a low-density lipoprotein cholesterol (LDL-C) level ≥3.37 mmol/L [1]. Hyperlipidemia is considered to be one of the major risk factors for the development of atherosclerosis and coronary heart disease (CHD) [2–4]. A recent meta-analysis demonstrated that a 1 mmol/L LDL-C decrease could result in a 21 % reduction in risk for a major vascular event [5]. Therefore, lipid-lowering therapy has significant value in preventing cardiovascular disease.

Statins are the most common drug used in lipid-lowering therapy. Of the Chinese population using lipid-lowering medications, 88.9 % of them used statins. However, only 61.5 % of the population reached the goal of decreased LDL-C [6]. There may be various reasons for this unsatisfied goal attainment. For instance, utilization of moderate/high-intensity statins is a common method for achieving the LDL-C goal. However, increasing the intensity of statins may lead to a high risk of adverse events, which results in low compliance and thus unsatisfactory goal attainment [7–9]. Moreover, in China, there is only one category of statin, simvastatin, which happens to be a low-intensity statin, on the National Essential Drugs List [10]. The high cost of other moderate/high-intensity statins may also limit their usage. Therefore, to help reach their goal attainment, many patients in China will seek help from Traditional Chinese Medicine (TCM).

Based on TCM theory, the generation of hyperlipidemia has a close relationship with the liver, spleen, kidney, and diet. The basic pathogenesis is phlegm-dampness stagnation and blood vessel obstruction by phlegm and blood stasis. Multiple reasons such as a deficiency of the spleen, over intake of greasy foods, and stagnation of the liver qi could lead to this pathological state. Therefore, according to the therapeutic principle of promoting blood circulation to remove blood stasis and promoting diuresis to eliminate dampness, the Yirui capsule is an innovative Chinese Medicine (CM) which could help hyperlipidemia patients to improve their blood lipid state.

The major contents of Yirui capsule include perilla oil, *Folium Ginkgo* (Yinxingye), *Radix Salviae miltiorrhizae* (Danshen), *Fructus Crataegi* (Shanzha), *Rhizoma Alismatis* (Zexie), and *Radix Notoginseng* (Sanqi). A modern pharmacological study showed that the main functional component of Yirui capsules was alpha-linolenic acid [11]. Recent studies have illustrated that alpha-linolenic acid could improve vascular inflammation and endothelial function and be helpful in secondary prevention of CHD [12–14]. The lipid-lowering effect of other herbal components has also been illustrated in animal experiments [15–19]. Possible mechanisms may relate to limitation of absorption, promotion of the metabolism, and transformation of blood lipids. As a Chinese Herbal Medicine, Yirui capsules could help prevent the generation of hyperlipidemia and regulate the blood lipid level. Two animal experiments have been completed and demonstrated that Yirui capsules could significantly reduce the LDL-C level in hyperlipidemic rat models [20, 21]. Nevertheless, there is still a lack of high-quality evidence from clinical trials to support the application. In the current study, we aim to demonstrate and assess the efficacy and safety of Yirui capsules in improving hyperlipidemia by using a randomized controlled trial (RCT). We chose simulant Yirui capsules which contained only a placebo as a comparator so that the actual lipid-lowering effect of the Yirui capsules could be evaluated.

The study was financially supported by Infinitus (China) Company Limited and was registered with an identifier (ChiCTR-IOR-15006496, 29 May 2015) in the Chinese Clinical Trial Registry (ChiCTR). This funding source had no role in the design of this study and will not have any responsibility during its execution, analyses, interpretation of the data, or decision to submit results.

## Methods/design

### Study design

This study is conducted as a double-blind, placebo-controlled trial with two parallel groups to examine the blood lipid-lowering effect of Yirui capsules. The protocol was developed according to Consolidated Standards of Reporting Trials (CONSORT) statement [22], Standard Protocol Items: Recommendations for Interventional Trials (SPIRIT) 2013 [23], and SPIRIT 2013 explanation and elaboration: guidance for protocols of clinical trials [24]. We plan to recruit 180 patients from the First Affiliated Hospital of Jinan University, Guangdong No. 2 Provincial People’s Hospital, Hexian Memorial Affiliated Hospital of Southern Medical University, and the Fifth Affiliated Hospital, Sun Yat-sen University. Clinical investigators from each center are responsible for screening eligible participants. After recruitment, participants are randomly and equally divided into two groups, the Yirui capsule group and the placebo group. Both arms will receive lifestyle modification therapy (decreasing the intake of saturated fatty acids and cholesterol, selecting foods which could reduce LDL-C, losing weight, increasing regular physical exercise, quitting smoking, limiting salt intake, etc.). Based on lifestyle modification, the Yirui group will receive Yirui capsules while the placebo group will receive simulant capsules. Then, the two arms will undergo a 24-week treatment and 4-week follow-up period. According to the China Food and Drug Administration guidelines [25], this 24-week treatment period was set based on our clinical experience and previous pilot studies. The participant flowchart is shown in Fig. 1, and the participant timeline is given in Table 1.

**Fig. 1 Fig1:**
[figure not shown]
Participant flowchart

**Table 1 Tab1:**
[figure not shown]
Schedule of enrollment, intervention, and assessments

There will be five visits for each participant in week 0, week 4, week 12, week 24, and week 28. At the first visit, patients will have their general data recorded and will be given the prescription. Then, patients will take the prescription to the specified pharmacy and receive either Yirui capsules or the placebo. 4 weeks and 12 weeks after the first visit, patients will come back for clinical evaluation and medication. Visit 4 is planned for the end of the treatment period (week 24); at this visit patients will only receive clinical evaluation. Afterwards, the patients will stop taking Yirui capsules or the placebo for another 4 weeks and then come back for clinical evaluation.

The study protocol was approved by the ethics committees of the First Affiliated Hospital of Jinan University, Guangdong No. 2 Provincial People’s Hospital, Hexian Memorial Affiliated Hospital of Southern Medical University, and the Fifth Affiliated Hospital, Sun Yat-sen University (Approval Version: LWXJ.YRJN-HBT-V1.0), and informed consent was obtained from each participant.

### Participants

#### Setting

The trial is conducted at the First Affiliated Hospital of Jinan University, Guangdong No. 2 Provincial People’s Hospital, Hexian Memorial Affiliated Hospital of Southern Medical University, and the Fifth Affiliated Hospital, Sun Yat-sen University. All participants are recruited from the public through the outpatient clinic.

#### Inclusion criteria

In this study, the inclusion criteria are as follows: (1) age of 18 to 65 years, both genders; (2) documented blood lipid test results indicated LDL-C ≥3.37 mmol/L complicated with TC ≥5.18 mmol/L, or triglyceride (TG) ≥1.70 mmol/L, or high-density lipoprotein cholesterol (HDL-C) <1.04 mmol/L, or both TC ≥5.18 mmol/L and TG ≥1.70 mmol/L; (3) initial treatment of hyperlipidemia; (4) signed informed consent and agreement to complete all visits, examinations, and treatments.

#### Exclusion criteria

Patients were excluded for one or more of the following reasons: (1) TG ≥5.65 mmol/L; (2) combined with hypertension, diabetes, or thyroid dysfunction; (3) combined severe primary diseases (i.e., cardiovascular and cerebrovascular diseases, liver and kidney diseases, hematopoietic system dysfunction), or malignant tumor, or mental disorder, or other serious complicated disease; (4) documented hyperlipidemia-induced target organ damage (i.e., atherosclerosis and CHD) with need to maintain treatment to dyslipidemia; (5) secondary hyperlipidemia, drug-induced hyperlipidemia, homozygous hypercholesterolemia; (6) pregnancy; (7) alanine aminotransferase (ALT) and/or aspartate aminotransferase (AST) ≥3 times the upper limit of normal (ULN); (8) creatinine (CREA) ≥1.5 times the ULN; (9) combined with active peptic ulcer or gastrointestinal hemorrhage; (10) allergy to components of product or allergic constitution; (11) hospitalized; (12) cannot obey therapeutic lifestyle modification.

### Interventions

#### Lifestyle modification

As mentioned above, every participant should practice therapeutic lifestyle modification. Specifically, the recommendations include reducing the intake of saturated fatty acids and cholesterol, choosing foods which could reduce LDL-C, losing weight, increasing regular physical exercise, smoking cessation, and limiting salt intake, etc. Diet evaluation should be conducted every week by the participant him/herself and the information documented in a diet diary card. The specific items are listed in Table 2.

**Table 2 Tab2:** Diet evaluation diary card

Items	Scoring
1. Did you eat meat <75 g/day in one recent week? 0 = No, 1 = Yes	
2. What kinds of meat did you eat: 0 = lean meat, 1 = fat lean meat, 2 = fat meat, 3 = innards	
3. How many eggs did you eat in one recent week? 1 = 0–3 eggs, 2 = 4–7 eggs, 3 = more than 7 eggs	
4. How many times did you eat fried food in one recent week? 0 = Not eaten, 1 = 1–4 times, 2 = 5–7 times, 3 = more than 7 times	
5. How many times did you eat brioches in one recent week? 0 = Not eaten, 1 = 1–4 times, 2 = 5–7 times	
Total	

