### Outcomes

Clinical investigators will obtain written informed consent and collect basic data such as gender, age, height, weight, and medical history at baseline. For safety concerns, besides the basic data, vital signs will be taken and laboratory examinations conducted, for instance, blood pressure, heart rate, routine blood tests (e.g., red blood cell (RBC), white blood cell (WBC), hemoglobin (Hb), etc.), liver and kidney function tests (e.g., ALT, AST, CREA, etc.), pregnancy test, and 12-lead electrocardiogram (ECG). Except for the pregnancy test, which only needs to be conducted in the first visit (week 0, baseline), other tests should be conducted routinely at every visit during the treatment period (the ECG is not mandatory at the second visit (week 4)). Also, any adverse events such as abdominal discomfort should be monitored and recorded during the whole study.

Participants need to receive a blood lipid profile test which contains the following indexes: TC, TG, HDL-C, LDL-C, apolipoprotein A (apoA), apolipoprotein B (apoB), and non-high-density lipoprotein cholesterol (non-HDL-C). The blood sample should be collected after at least a 12-hour fast, and the last meal before the blood sampling should not contain greasy food. In order to evaluate the health status of participants, the MOS 36-Item Short-Form Health Survey (SF-36) is utilized [26–28]. In addition, for assessment of clinical symptoms, another symptomatic grading and quantifying scale is applied. Weight monitoring and diet evaluation are also two aspects that need to be conducted. All participants are required to complete the tests and scales mentioned above at every visit under the guidance and assistance of the clinical investigators. The results are recorded and compared within a group and between groups before and after intervention.

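### Item 1 of the diet diary card is scored in the opposite direction to items 2–5, so it partly offsets them in the diet total (minor)

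*Protocol article*

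**What the plan says.** The Lifestyle modification section has every participant assess their diet weekly on the card in Table 2. It sets the favourable direction: "the recommendations include reducing the intake of saturated fatty acids and cholesterol".

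The card's items are coded as follows:

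- Item 1: "Did you eat meat <75 g/day in one recent week? 0 = No, 1 = Yes".
- Item 2: "What kinds of meat did you eat: 0 = lean meat, 1 = fat lean meat, 2 = fat meat, 3 = innards".
- Item 3: "How many eggs did you eat in one recent week? 1 = 0–3 eggs", rising to 3 for more than 7 eggs.
- Item 4: "How many times did you eat fried food in one recent week? 0 = Not eaten", rising to 3 for more than 7 times.
- Item 5: "How many times did you eat brioches in one recent week? 0 = Not eaten", rising to 2 for 5–7 times, with no code above that.

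A single total row closes the table. Nothing says that any item is to be reversed, or whether a high or a low total is good.

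The Outcomes section lists diet evaluation among the assessments made at each visit and ends: "The results are recorded and compared within a group and between groups before and after intervention". The section on data collection and withdrawal makes completing the card compulsory. Diet score is not the primary outcome, is not among the listed secondary outcomes, and is not mentioned under Statistical analysis.

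**The concern.** A summed score has a clear meaning only if all its items point the same way. Here four items add points for a worse diet and one adds a point for a better one. No choice of direction for the total makes all five agree.

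Both arms receive lifestyle therapy, part of which is meant to lower LDL-C, and the card is the only diet measure the article describes. If its total is used to see whether diet was similar in the two arms, or changed over time, participants with low meat intake will look slightly worse than they should, and those with high intake slightly better.

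**Working it through.** The article gives no range, cut-off or direction for the total, so there is no stated figure to reproduce. The check uses only the codes in Table 2 and takes the total as the plain sum of the items.

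**Inputs (Table 2).** Item 1 takes 0–1, item 2 takes 0–3, item 3 takes 1–3, item 4 takes 0–3 and item 5 takes 0–2. That gives 2 × 4 × 3 × 4 × 3 = 288 answer patterns, all of which were enumerated.

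**Formulas.** Let x be the item 1 code (1 = under 75 g/day) and S the sum of items 2–5.

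- Printed total: T = x + S
- Consistent total: T′ = (1 − x) + S = T + 1 − 2x

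S runs from 0 + 1 + 0 + 0 = 1 to 3 + 3 + 3 + 2 = 11, a span of 10 points. Both T and T′ run from 1 to 12.

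| Pattern | Printed T | Consistent T′ |
|---|---|---|
| Best on every item (x = 1, S = 1) | 2 | 1 |
| Best on items 2–5, meat threshold exceeded (x = 0, S = 1) | 1 | 2 |
| Worst on every item (x = 0, S = 11) | 11 | 12 |
| Worst on items 2–5, under the meat threshold (x = 1, S = 11) | 12 | 11 |

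**Individual level.** Every printed total is off by exactly 1 point: T′ − T is −1 when x = 1 and +1 when x = 0. The effect of staying under 75 g/day is +1 as printed and −1 when coded consistently, a swing of 2 points on a scale 11 points wide (12 − 1).

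**Group level.** Suppose one arm has a proportion d more participants under 75 g/day and the arms are equal on items 2–5. The difference in mean total is +d as printed and −d when consistent, a discrepancy of 2d. The article gives no figure for d, so a range is assumed:

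| Assumed d | Printed difference | Consistent difference | Discrepancy |
|---|---|---|---|
| 0.10 | +0.1 | −0.1 | 0.2 |
| 0.20 | +0.2 | −0.2 | 0.4 |
| 0.30 | +0.3 | −0.3 | 0.6 |

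If d = 0, the between-arm difference is unaffected.

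**The other two irregularities.** Item 3 starts at 1, which adds the same constant to every total and drops out of every within-group and between-group difference. Item 5 has no code for more than 7 times although item 4 has one. That is a small, separate gap.

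**The case against.** The strongest reply is that little depends on this total. The general sentence in Outcomes covers lipids, quality of life, symptoms, weight and diet together, and nowhere says that the diet total is the quantity compared; that use is inferred from the total row. The purpose of checking lifestyle balance is likewise not stated. Comparability of the arms rests on randomization and blinding, not on this card, and the item-level answers remain usable. All of this stands and limits the weight of the point.

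A second reply is that Table 2 may misprint or mistranslate the card that participants receive. That is possible. It means no data should be recoded before the card in use has been seen, because recoding a correct card would introduce the error.

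That a journal article condenses the full protocol does not help here: the card is printed with its codes, and those codes conflict.

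Three stronger readings are tempting and are not supported:

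- That item 1 cancels the other items. It moves the total by at most 1 point, against a 10-point span for items 2–5, so it only partly offsets them.
- That the card cannot reveal unequal diet between arms, or that the LDL-C result is compromised. The discrepancy is 0.2–0.6 points over the assumed range, and no listed outcome uses the score.
- That item 3's starting value biases comparisons. A constant cannot.

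**Conclusion.** The point holds as a minor scoring error. As printed, Table 2 gives a diet that is best on every item a worse total (2) than the same diet with the meat threshold exceeded (1), and gives its maximum of 12 to someone who stays under the threshold. The contribution of item 1 is wrong by 2 points relative to consistent coding. The error in a between-arm mean is twice the difference in the proportions under 75 g/day.

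This rests on three assumptions: the card in use matches Table 2; the total is the plain sum; and less meat is the favourable answer, which follows from the stated aim of reducing saturated fat and cholesterol. It matters only if the total is in fact compared within or between groups. The LDL-C primary outcome and the listed secondary outcomes are unaffected.

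**What to change.** 1. Check the wording and codes of the card that participants complete.
2. If they match Table 2, reverse item 1 at analysis on all cards (1 minus the recorded value). If they do not, correct the published table and leave the data alone.
3. State that a lower total means a better diet.
4. Leave item 3 as it is. Rebasing it to 0–2 on new cards only would create a 1-point artefact between card versions, as large as the whole range of item 1.
5. If a code for more than 7 times is added to item 5, merge it with the 5–7 category when computing the total, so that old and new cards stay comparable. This presumes that participants above 7 chose the top category on the old card.

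The cost is one look at the card, one recoding line if needed and one sentence on direction; no new data are required. Trial status reports that nobody had completed treatment at submission, so at that stage the correction could still be settled before analysis.

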#### Chinese Medicine intervention

The Yirui capsule is composed of perilla oil, *Folium Ginkgo* (Yinxingye), *Radix Salviae miltiorrhizae* (Danshen), *Fructus Crataegi* (Shanzha), *Rhizoma Alismatis* (Zexie), and *Radix Notoginseng* (Sanqi). The specific Chinese herbal medicine composition and actions are summarized in Table 3. The placebo capsule was a simulant Yirui capsule with a comparable appearance. The main content of the placebo capsule was starch. By adding food colorants and flavoring agents, the mixture achieved a color, smell, taste, and texture comparable to the content of the Yirui capsule. Participants from both the Yirui group and the placebo group were informed to take two assigned capsules orally twice daily for 24 weeks continuously. Both Yirui capsules and the placebo were packed in sealed plastic bottles (120 capsules each). Only the serial number was printed outside the package to ensure successful blinding of patients.

**Table 3 Tab3:** Composition and action of Chinese herbal medicine in Yirui capsule

Ingredients	Action
*Folium Ginkgo*	TCM: Promoting blood circulation to remove blood stasis and stop pain Pharmaceutical study: (1) cardiovascular protective effect, (2) hypolipidemic effect, (3) effect of antagonizing lipid peroxide, (4) effect of improving cerebral circulation
*Radix Salviae miltiorrhizae*	TCM: Promoting blood circulation to remove blood stasis, cooling blood and treating boils, tranquilizing mind Pharmaceutical study: (1) cardiovascular protective effect, (2) hypotensive effect, (3) hypolipidemic effect, (4) anti-inflammatory effect, (5) anti-coagulation effect
*Fructus Crataegi*	TCM: Removing food retention and flatulence, promoting blood circulation to remove blood stasis Pharmaceutical study: (1) gastrointestinal regulation effect, (2) cardiovascular protective effect, (3) hypotensive effect, (4) hypolipidemic effect
*Rhizoma Alismatis*	TCM: Eliminating dampness and diuresis, purging heat Pharmaceutical study: (1) diuretic effect, (2) hypolipidemic effect, (3) anti-allergic effect, (4) anti-inflammatory effect
*Radix Notoginseng*	TCM: Hemostatic elimination of stagnation, promoting blood circulation to stop pain Pharmaceutical study: (1) Anti-coagulation effect, (2) hematopoiesis effect, (3) cardiovascular protective effect, (4) analgesic effect, (5) anti-inflammatory effect

